# Protocol for TRAUMADORNASE: a prospective, randomized, multicentre, double-blinded, placebo-controlled clinical trial of aerosolized dornase alfa to reduce the incidence of moderate-to-severe hypoxaemia in ventilated trauma patients

**DOI:** 10.1186/s13063-020-4141-6

**Published:** 2020-03-18

**Keywords:** Acute respiratory distress syndrome, Adult, Hypoxaemia, Multiple trauma, Deoxyribonuclease I, Neutrophil extracellular traps, Randomized controlled trial

## Abstract

**Background:**

Acute respiratory distress syndrome continues to drive significant morbidity and mortality after severe trauma. The incidence of trauma-induced, moderate-to-severe hypoxaemia, according to the Berlin definition, could be as high as 45%. Its pathophysiology includes the release of damage-associated molecular patterns (DAMPs), which propagate tissue injuries by triggering neutrophil extracellular traps (NETs). NETs include a DNA backbone coated with cytoplasmic proteins, which drive pulmonary cytotoxic effects. The structure of NETs and many DAMPs includes double-stranded DNA, which prevents their neutralization by plasma. Dornase alfa is a US Food and Drug Administration-approved recombinant DNase, which cleaves extracellular DNA and may therefore break up the backbone of NETs and DAMPs. Aerosolized dornase alfa was shown to reduce trauma-induced lung injury in experimental models and to improve arterial oxygenation in ventilated patients.

**Methods:**

TRAUMADORNASE will be an institution-led, multicentre, double-blinded, placebo-controlled randomized trial in ventilated trauma patients. The primary trial objective is to demonstrate a reduction in the incidence of moderate-to-severe hypoxaemia in severe trauma patients during the first 7 days from 45% to 30% by providing aerosolized dornase alfa as compared to placebo. The secondary objectives are to demonstrate an improvement in lung function and a reduction in morbidity and mortality. Randomization of 250 patients per treatment arm will be carried out through a secure, web-based system. Statistical analyses will include a descriptive step and an inferential step using fully Bayesian techniques. The study was approved by both the Agence Nationale de la Sécurité du Médicament et des Produits de Santé (ANSM, on 5 October 2018) and a National Institutional Review Board (CPP, on 6 November 2018). Participant recruitment began in March 2019. Results will be published in international peer-reviewed medical journals.

**Discussion:**

If early administration of inhaled dornase alfa actually reduces the incidence of moderate-to-severe hypoxaemia in patients with severe trauma, this new therapeutic strategy may be easily implemented in many clinical trauma care settings. This treatment may facilitate ventilator weaning, reduce the burden of trauma-induced lung inflammation and facilitate recovery and rehabilitation in severe trauma patients.

**Trial registration:**

ClinicalTrials.gov, NCT03368092. Registered on 11 December 2017.

## Administrative information

Note: the numbers in curly brackets in this protocol refer to SPIRIT checklist item numbers. The order of the items has been modified to group similar items (see http://www.equator-network.org/reporting-guidelines/spirit-2013-statement-defining-standard-protocol-items-for-clinical-trials/).

**Table Taba:** 

Title {1}	Protocol for TRAUMADORNASE: a prospective, randomised, multicentre, double-blinded, placebo-controlled clinical trial of aerosolized dornase alfa to reduce the incidence of moderate to severe hypoxemia in ventilated trauma patients
Trial registration {2a and 2b}	ClinicalTrials.gov NCT03368092
Protocol version {3}	8.0, November 13, 2018
Funding {4}	Aerogen (Ireland) will provide nebulizers to study centres at an estimated value of 28k€. After validation from its Scientific Committee, the TRAUMADORNASE study is supported by a 300k€ grant from the French Ministry of Health (PHRCI-2017-S09).

Role of sponsor {5c}	Funders will have no role in the study’s design, collection, management, analysis, interpretation of data, writing of the report, and the decision to submit the report for publication.

## Introduction

### Background and rationale {6a}

Severe trauma remains a major socio-economic burden worldwide [1, 2]. Indeed, it is the third cause of fatality overall, the first cause of fatality and invalidity in the 16–45 age group and the first cause of disability-adjusted life years (DALYs). Aside from civilian and military trauma cases, terrorist attacks have added new threats [3]. While the first peak of trauma-associated mortality happens within the very first hours from exsanguination and severe central nervous system injuries, secondary deaths are triggered by multi-organ failure (MOF) and acute respiratory distress syndrome (ARDS) in the intensive care unit (ICU) [4].

The taxonomy of ARDS was recently refined by the last Berlin definition [5], which also distinguished three levels of increasing hypoxaemia severity (mild/moderate/severe) based on the ratio of partial arterial oxygen tension (PaO_2_) over inspired oxygen fraction (FiO_2_). Patients who develop moderate-to-severe ARDS in the ICU have a worse prognosis compared to mild ARDS patients, including increased mortality rates (48% vs*.* 29%), impaired functional recovery, compromised quality of life and cognitive dysfunction [6]. Severe trauma definitely remains a significant risk factor for hypoxaemia, implicating both direct and indirect lung injuries [7]. Notwithstanding improvements in prehospital care, resuscitation and mechanical ventilation, the incidence of hypoxaemia in trauma patients has remained consistently high during the last 30 years [8–11]. In the most severely injured trauma patients (Injury Severity Score (ISS) [12] above 15) requiring blood transfusion, the incidence of hypoxaemia may exceed 40%. Indeed, a recent analysis of the PROMMTT registry underlines that the incidence of moderate-to-severe hypoxaemia could be as high as 45% [13]. In trauma patients, ARDS increases the duration of mechanical ventilation, ICU and hospital lengths of stay, incidence of ventilation-acquired pneumonias, healthcare-associated costs and mortality [14].

### Pathophysiology of trauma-associated hypoxaemia and acute respiratory distress syndrome

As previously stated [7], severe trauma may contribute to hypoxaemia by both direct injuries (lung contusion, aspiration) and indirect injuries (non-thoracic trauma, musculoskeletal injuries, haemorrhagic shock, transfusion-associated acute lung injury [15, 16]). Whatever the mechanism implicated, inflammation is a key player [17–19]. Indeed, tissue injury triggers a massive and short-lived release of damage-associated molecular patterns (DAMPs) [20], which bind both Toll-like receptors (TLRs) [21] and receptors for advanced glycation end products (RAGE) [22, 23], which recruit and activate neutrophils, resulting in a widespread systemic inflammatory response [24].

The molecular structure of DAMPs is diverse but the most potent are made of double-stranded DNA [25], either fully (e.g. mitochondrial DNA [26–28]) or partly (e.g. nucleosomes [29], high mobility group box-1 (HMGB1), heat shock proteins (HSP)).

Once bound to neutrophils, DAMPs induce profound conformational changes in these cells (NETosis), which trigger both non-self pathogen killing [30] and self tissue injury [22, 31]. Indeed, NETosis refers to the release of neutrophil extracellular traps (NETs), composed of a backbone (decondensed chromatin fibres) coated with antimicrobial granular and cytoplasmic proteins, such as myeloperoxidase, neutrophil elastase (NE) and α-defensins [32, 33]. The detrimental effects of excessive NET release are particularly important to ARDS, because NETs can expand more easily in the pulmonary alveoli, causing extensive lung injury [33] and hypoxaemia. Moreover, while unbound NE is usually rapidly inactivated when released into plasma, DNA-bound NE is protected from neutralization by plasma [34].

Double-stranded DNA thus constitutes the backbone of both DAMPs and NETs, and prevents NETs from plasma neutralization. Extracellular DNA is physiologically broken up by endogenous deoxyribonucleases (DNases [33, 35]), which may become overwhelmed by a massive influx of both DAMPs and NETs. This is exacerbated as the activity of endogenous DNases is reduced in severe trauma patients (0.059 ± 0.0033 U/ml) compared to healthy controls (0.174 ± 0.031 U/ml; *p* < 0.0001 [36]).

However, an FDA-approved recombinant DNase has been commercially available since 1994 (dornase alfa, Pulmozyme; Roche, Basel, Switzerland and Genentech, San Francisco, CA, USA) and prescribed for the treatment of pulmonary exacerbations in cystic fibrosis patients. As dornase alfa is usually administered via the intratracheal route (aerosols), its biological actions and pharmacokinetic properties could be an excellent prerequisite for a clinical breakthrough in trauma-induced hypoxaemia. Indeed, dornase alfa was shown to reduce trauma-induced lung injury in mice [37], to fight against sepsis-induced ARDS [38, 39] and to reduce mechanical ventilation-induced lung injury [40], which are traditional “second hits” for lung damage in ventilated trauma patients. In a small, randomized clinical trial, aerosolized dornase alfa was also shown to improve oxygenation in mechanically ventilated ICU patients with lobar atelectasis [41].

### Objectives {7}

#### Primary objective

The primary objective of the TRAUMADORNASE study is to demonstrate a reduction in the incidence of moderate-to-severe hypoxaemia from 45% to 30% in severe trauma patients during the first 7 ICU days by providing aerosolized dornase alfa once during the first 2 ICU days as compared to equivalent provision of placebo (NaCl 0.9%).

#### Secondary objectives

The secondary objectives are to demonstrate, using aerosolized dornase alfa as compared to placebo, an improvement in static lung compliance, a reduction in mechanical ventilation duration or an increase in ventilation-free ICU days, a reduction in the length of ICU stay, a reduction in the hospital length of stay, a reduction in the incidence of multi-organ failure, a reduction in the incidence of ventilator-associated pneumonia (VAP) and a reduction in mortality at day 30.

### Trial design {8}

This will be an investigator-initiated, institution-led, multicentre, double-blinded, placebo-controlled, parallel-group, superiority, randomized trial in ventilated, trauma ICU patients.

Randomization will be carried out through a secure web-based randomization system, stratified by the centre and the presence of severe traumatic brain injury (Glasgow Coma Score < 9 on scene).

## Methods: participants, interventions and outcomes

### Study setting {9}

The study will be conducted in seven French participating hospitals, both university-affiliated and non-university-affiliated.

### Eligibility criteria {10}

Inclusion criteria will be checked before inclusion in the study.

The inclusion criteria are as follows:
Adult patient (> 18 years old) of either sex affiliated to the National Health ServiceSevere trauma patient (either blunt or penetrating) with ISS [12] > 15Under mechanical ventilation for an expected duration > 48 hAdmitted to the ICUSigned informed consent from the patient or the patient’s relative or emergency consent procedurePatient equipped with an indwelling arterial catheterNegative pregnancy test in women of childbearing age

The exclusion criteria are as follows:
Pregnancy or breast-feedingOpposition from the patient or his/her relativesProtected major (Guardianship)Contraindication to the use of dornase alfaKnown intolerance to dornase alfaPatient whose life expectancy is less than 24 h, according to the treating physician“Do not resuscitate” order

### Who will take informed consent? {26a}

Inclusion will be feasible after patient approval, relative approval or emergency consent procedure (according to French law [42]).

Subsequent confirmation of consent will be obtained from the relatives and from the patient as soon as possible. The consent forms are available from the corresponding author on request.

After primary haemostasis and emergent surgical interventions, patients will be randomized in the ICU within 6 h. In the case of emergent surgical intervention before ICU admission, a maximum delay of 18 h will be tolerated from hospital admission (trauma bay) to study drug administration. Day 0 will be considered the day of ICU admission.

### Additional consent provisions for collection and use of participant data and biological specimens {26b}

Additional consent will be required for the collection of biological specimens in ancillary studies, which will be stored for a maximum duration of 15 years.

### Interventions

#### Explanation for the choice of comparators {6b}

The comparator will be normal saline (NaCl 0.9%, 2.5 ml, administered through the Aerogen solo device). NaCl is neutral regarding DAMPs, NETs and occurrence of either hypoxaemia or ARDS, and therefore is considered a placebo.

#### Intervention description {11a}

Treatment with either dornase alfa or placebo will be administered using aerosol (Aerogen solo) in the ventilation circuit once per day (average treatment length: 7 min) for the first 2 days. The Aerogen device was shown to optimize dornase alfa deposition in the distal lung airways [43, 44]. Dornase alfa has an excellent safety profile and aerosolized NaCl 0.9% has a neutral effect on lung physiology.

The variables under study will be gathered every day and recorded on the electronic clinical research form (CleanWeb; Telemedicine Technologies S.A.S., Boulogne Billancourt, France).

For safety purposes, patient variables will be closely monitored before, during and within the first post-administration hour: lowest SpO_2_, maximal value and maximal increase in peak inspiratory airway pressure, maximal value and maximal increase in plateau airway pressure, extreme values of heart rate and mean arterial pressure, skin erythema, urticaria and variations in central temperature exceeding 1 °C.

During the first 7 days, at least one blood gas analysis and chest X-ray will be performed every day at 8:00 a.m. to compute the primary endpoint: presence or absence of ARDS and severity of hypoxaemia according to the Berlin definition. Additional blood gas analysis will be allowed and the worst daily PaO_2_/FiO_2_ ratio will be considered.

#### Ancillary mechanistic study

On days 0, 3 and 5, additional blood samples (6 ml on each day) will be drawn into EDTA tubes, centrifuged and stored (− 80 °C) for subsequent analysis of DAMPs (mitochondrial DNA by qPCR; HMGB1, HSP70 and sRAGE by ELISA) at the end of enrolment. Whole blood samples will be drawn (days 0, 3 and 5) for extemporaneous quantification of NETs on fresh blood using a flow cytometric assay [45] in patients at the Strasbourg centre.

### Criteria for discontinuing or modifying allocated interventions {11b}

In the case of an adverse event following treatment administration (desaturation, bronchospasm, anaphylactic reaction), treatment will be immediately discontinued and the second treatment dose will not be given on day 1.

### Strategies to improve adherence to interventions {11c}

In each centre, boxes containing both full and empty treatment vials will be returned to the pharmacy responsible for clinical studies. For every included patient, a sheet will be completed (date, hour, nurse in charge) and signed for every study treatment preparation, administration and clinical surveillance.

For safety purposes, patient variables will be closely monitored before, during and within the first post-administration hour: lowest SpO_2_, maximal value and maximal increase in peak inspiratory airway pressure, maximal value and maximal increase in plateau airway pressure, extreme values of heart rate and mean arterial pressure, skin erythema, urticaria and variations in central temperature exceeding 1 °C.

At least one blood gas analysis and chest X-ray will be performed every day at 8:00 a.m. to compute the primary endpoint: presence or absence of ARDS and severity of hypoxaemia according to the Berlin definition. Additional blood gas analysis will be allowed and the worst daily PaO_2_/FiO_2_ ratio will be taken into account.

### Relevant concomitant care permitted or prohibited during the trial {11d}

#### Standardization of respiratory care

Daily care for the included patients will be protocolized according to good clinical practices, especially concerning respiratory care (semi-recumbent position, protective mechanical ventilation (6–8 ml/kg predicted body weight), PEEP > 5 cmH_2_O, plateau pressure < 30 cmH_2_O, close tracheal cuff pressure monitoring, early enteral feeding (500 ml on day 1), glucose control and protocolized sedation based on both CPOT and RASS scores [46]). Adherence to guidelines will be checked in every centre for every patient.

Patients will be followed until day 30 for the record of study outcomes.

Every concomitant care will be allowed except aerosols during study drug administration.

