### Outcomes {12}

#### Primary endpoint

The primary endpoint will be the incidence of moderate-to-severe hypoxaemia (PaO_2_/FiO_2_ < 200, according to the Berlin definition [5]) in severe trauma patients (ISS > 15) during the first 7 ICU days. The PaO_2_/FiO_2_ ratio will be computed at least once daily (8:00 a.m.) together with the supine chest X-ray and the worst daily PaO_2_/FiO_2_ value will be taken into account to define hypoxaemia severity. In ARDS patients, the severity of hypoxaemia allows for its classification according to the Berlin definition and is strongly associated with mortality, length of recovery and quality of life [6, 7].

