### Participant timeline {13}

The total duration of participation in the study will be 30 days. The forecast study duration is 36 months from first to last patient recruitment (Table 1).

**Table 1 Tab1:** Template of recommended content for the schedule of enrolment, interventions and assessments

	Visit				
	Information	Enrolment	Allocation, visit 0	Post-allocation, visits 1–7	Close-out
Timepoint	Day 0	Day 0	Day 0	Days 1–7	Day 30
Location	Hospital	Hospital	Hospital	Hospital	Hospital
Next of kin information	X*	X*	X		
Signed informed consent		X*			
Plasma **β**HCG assay		X(*)			
Eligibility criteria check	X*	X*	X*		
Randomization			X*		
Study drug administration			X*^d^	X*^d^	
Clinical examination^a^		X	X	X	
Diagnostic tests^b^		X	X	X	
Blood assay^c^			X*	X*	
Adverse effect recording		X*	X*	X*	X*
Concomitant medications		X	X	X	X

*βHCG* beta human chorionic gonadotropin, *X* diagnostic test performed on a daily basis according to the standard of care in participating centres, *X** diagnostic tests performed for the purpose of the TRAUMADORNASE study

^a^Clinical examination includes physical examination (auscultation of the chest, central body temperature, positive end-expiratory pressure and inspired oxygen fraction levels) and recording of Utstein criteria [49]

^b^Diagnostic tests include arterial blood gases, chest X-ray, leukocyte and platelet counts, creatinine, blood urea nitrogen, bilirubin and quantitative lung bacteriologic samplings (bronchoalveolar lavage fluid or protected specimen brush) in the case of suspected lung infection

^c^Blood withdrawal: 6 ml of blood on day 0, day 3 and day 5

^d^Study treatment will be given on day 0 and day 1

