### Assignment of interventions: blinding

#### Who will be blinded {17a}

Trial participants, care providers, outcome assessors and data analysts will remain blinded after assignment to interventions, until the final analysis.

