#### Methods for additional analyses (e.g. subgroup analyses) {20b}

Analyses will be performed in intention to treat. To verify the impact of possible deviations from the protocol, these analyses will be supplemented by an analysis per protocol. Subgroup analyses will be conducted according to the Glasgow Coma Scale on site (score either ≤ 8 or > 9).

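### Non-study dornase alfa is permitted care during the 7-day endpoint window, so placebo patients may receive the study drug without a protocol deviation

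*Protocol article*

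**What the plan says.** **Concomitant care.** Under Standardization of respiratory care {11d}, the article states: "Every concomitant care will be allowed except aerosols during study drug administration". The same section sets standards for positioning, ventilation, feeding, glucose control and sedation. It does not mention mucolytics or DNase.

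**Study dosing.** Intervention description {11a} gives the aerosol "once per day (average treatment length: 7 min) for the first 2 days". The footnote to Table 1 fixes the days: "Study treatment will be given on day 0 and day 1".

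**Eligibility {10}.** Dornase alfa appears in two exclusion criteria, one for contraindication and one for known intolerance. Current or recent use is not an exclusion.

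**Primary endpoint {12}.** The endpoint is a PaO2/FiO2 ratio below 200 at any time in the first 7 ICU days. The worst daily "value will be taken into account to define hypoxaemia severity".

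**Recording, blinding and deviations.** Table 1 lists "Concomitant medications" among the items collected through day 30. Section {17a} says: "Trial participants, care providers, outcome assessors and data analysts will remain blinded after assignment to interventions". Section {20b} makes intention to treat the main analysis and adds: "To verify the impact of possible deviations from the protocol, these analyses will be supplemented by an analysis per protocol".

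**The concern.** The trial compares dornase alfa with saline, and that contrast depends on placebo patients not receiving dornase alfa from another source before the endpoint is settled. The product is on the market. The article's own background reports that a small randomised trial found better oxygenation in ventilated ICU patients with lobar atelectasis. A clinician treating a ventilated trauma patient with collapse therefore has a documented reason to prescribe it. Because clinicians are blinded, they cannot know whether the patient has already had it.

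If a placebo patient is treated before PaO2/FiO2 drops below 200, that patient's risk of the event may fall and the difference between arms shrinks. Use after the drop cannot change the primary endpoint. It could still affect ventilation duration, ICU stay, lung compliance and the day 3 and day 5 biomarker comparisons.

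This is more than a detail left out of a condensed article. The section states positively that everything is allowed apart from one narrow exception, so a site following it may give the drug.

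**Working it through.** **Step 1. How much of the window does the bar cover?**

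- Barred time, literal reading: 2 doses × 7 min = 14 min {11a}.
- Endpoint window: 7 × 24 × 60 = 10,080 min {12}.
- Share: 14 / 10,080 = 0.14%.

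On a wider reading, the bar would cover the whole of dosing days 0 and 1. The rest of the window, from day 2, is still open.

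**Step 2. Does another section close the gap?**

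- Eligibility {10}: no. A current user without contraindication or intolerance can be enrolled.
- Respiratory-care standards {11d}: no. They say nothing on this drug.
- Table 1: no. It records medication but does not restrict it.
- Per-protocol analysis {20b}: no. It addresses deviations, and care that {11d} permits is not a deviation.

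**Step 3. The plan's own sample size.** Section {14} expects 0.45 against 0.30 and arrives at 200 per arm, raised to 250. It is a Bayesian sizing with no stated decision threshold, alpha or power, so 200 cannot be uniquely reproduced. The closest frequentist match is 199 per arm (two-sided 0.05, 85% power, continuity correction). The finding does not depend on this figure. The power values below are a frequentist stand-in for the Bayesian plan.

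**Step 4. Dilution.** Let c be the share of placebo patients given non-study dornase alfa. Let f be the share of that use that comes before an event and has the full study-drug effect. Both are assumptions, since the documents give neither. Extra drug in the active arm is assumed to add nothing; if it did add benefit, dilution would be smaller.

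- Placebo rate = 0.45 − 0.15 × c × f
- Difference = 0.15 × (1 − c × f)

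**Step 5. Proxy power.** The test is two-sided at 0.05 with the pooled normal approximation and the active arm at 0.30:

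Power = Φ[(difference − 1.96 × SE0) / SE1], where SE0 = √(2p̄(1 − p̄)/n), p̄ is the mean of the two rates, and SE1 = √(p1(1 − p1)/n + p2(1 − p2)/n).

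Worked example for c = 0.10, f = 1, n = 200: p1 = 0.435, p2 = 0.30, p̄ = 0.3675, SE0 = 0.0482, SE1 = 0.0477. Power = Φ[(0.135 − 1.96 × 0.0482) / 0.0477] = 80.2%.

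| c | f | Difference (points) | Power, 200 per arm | Power, 250 per arm |
|---|---|---|---|---|
| 0 | – | 15.0 | 87.5% | 93.6% |
| 5% | 1 | 14.25 | 84.1% | 91.2% |
| 10% | 1 | 13.5 | 80.2% | 88.1% |
| 5% | 0.5 | 14.6 | 85.9% | 92.5% |
| 10% | 0.5 | 14.25 | 84.1% | 91.2% |

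Bringing the difference down to the 0.12 named in {14} would take full-effect use before an event in 20% of placebo patients: 0.15 × (1 − 0.20) = 0.12. Proxy power would then be 70.7% at 200 per arm.

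**The case against.** The strongest reply is that the harm is hypothetical and small.

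- No section gives a use rate. The article names cystic fibrosis as the prescribed use, so routine use in trauma patients is unlikely. **This stands**, and every percentage above is an assumption.
- The clinical reason for use is atelectasis, so prescribing would tend to follow worsening oxygenation. Some of it would come after the endpoint is already met. **This stands** and makes f = 1 an upper bound.
- The background describes a short-lived release of damage signals, and the strategy rests on early treatment. Rescue use from day 2 might not reproduce the full effect. **This stands** and lowers f further.
- Even at 10% use with full effect, proxy power remains 80.2% at 200 per arm. **This stands.**
- Prescribers are blinded, respiratory care is standardised with adherence checked, and medications are recorded. **This stands only in part.** Blinding prevents use from being aimed at one arm, and recording makes use visible. None of these stops a placebo patient from receiving the drug.
- Allowing rescue care equally in both arms is a legitimate treatment-policy choice. **This does not settle the point.** Here the permitted care includes the investigational product itself, and the article presents no rationale for allowing that.
- The bar could mean the dosing days rather than the nebulisations. **This narrows the gap but does not close it.**

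**Conclusion.** The concern holds. As written, non-study dornase alfa is permitted during nearly all of the 7-day endpoint window, current users are eligible, and use would not count as a deviation. Any effect on the primary comparison runs towards the null, and there is no risk of a false positive from this source.

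The size is unknown and probably small. With 5% to 10% use among placebo patients, the planned difference loses at most 0.75 to 1.5 points and proxy power at 200 per arm loses 3.4 to 7.3 percentage points. With half of that use effective, the losses are about 0.4 to 0.75 points and 1.6 to 3.4 percentage points. These figures rest on assumed use rates, a frequentist proxy for a Bayesian plan, and no added benefit from extra drug in the active arm.

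The article itself calls the 15-point reduction ambitious, so avoidable dilution is worth preventing when the remedy is this cheap. It should be changed, but it does not threaten the trial's validity.

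**What to change.** 1. **Eligibility {10}:** add an exclusion for patients receiving dornase alfa at screening.
2. **Concomitant care {11d}:** add a second exception to the rule, so that it also bars *non-study dornase alfa from randomisation to day 7*.
3. **Data collection (Table 1):** make non-study dornase alfa a named item, with date and time, within the concomitant medications already collected. Report any use by arm as a protocol deviation.

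The primary analysis and sample size need no change, because intention to treat already keeps these patients in. Once use counts as a deviation, the per-protocol analysis may drop them. That result should be read as supportive only: use prompted by worsening oxygenation is informative, and excluding those patients would selectively remove the ones who deteriorate.

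The cost is one eligibility line, one clause and one case-report-form item. Clinicians give up a seldom-used off-label option for 7 days, and very few patients become ineligible.
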